# The (cost) effectiveness of a very low-energy diet intervention with the use of eHealth in patients with type 2 diabetes and obesity: study protocol for a randomised controlled non-inferiority trial (E-diet trial)

**DOI:** 10.1186/s13063-023-07620-6

**Published:** 2023-10-05

**Keywords:** Type 2 diabetes, Overweight, Obesity, Diet, Very low energy diet, eHealth, Mobile application, Blended care, Non-inferiority

## Abstract

**Background:**

Despite preventive measures, the number of people with type 2 diabetes and obesity is increasing. Obesity increases morbidity and mortality in people with type 2 diabetes, making weight loss a cornerstone of treatment. We previously developed a very low energy diet (VLED) intervention that effectively reduced weight in people with type 2 diabetes in the long term. However, this intervention requires considerable time and manpower, which reduces the number of people who can benefit from it. eHealth offers more efficient solutions but has proven to be less effective than face-to-face interventions. Therefore, we want to investigate whether a blended version of our VLED intervention (in which face-to-face contact is partly replaced by an eHealth (mobile) application (E-VLED)) would be more cost-effective than the current face-to-face intervention.

**Methods:**

We will conduct a randomised, controlled trial with non-inferiority design in patients with type 2 diabetes and obesity (BMI > 30 kg/m^2^), aged 18–75 years. The control group will receive the usual care VLED intervention, while the intervention group will receive the E-VLED intervention for 1 year, where face-to-face contact will be partly replaced by an eHealth (mobile) application. The main study endpoint is the difference in weight (% change) between the control and intervention group after 1 year, plus the difference between the total costs (euro) of the treatment in the control and intervention groups. The secondary aims are to investigate the effectiveness of the E-VLED diet intervention regarding cardiovascular risk factors, quality of life, patient satisfaction, compliance, and to study whether there is a difference in effectiveness in pre-specified subgroups. General linear models for repeated measurements will be applied for the statistical analysis of the data.

**Discussion:**

We hypothesise that the E-VLED intervention will be equally effective compared to the usual care VLED but lower in costs due to less time invested by the dietician. This will enable to help more people with type 2 diabetes and obesity to effectively lose weight and improve their health-related quality of life.

**Trial registration:**

Netherlands Trial Register, NL7832, registered on 26 June 2019.

## Introduction

### Background and rationale {6a}

Type 2 diabetes (T2D) affects 422 million adults worldwide, of whom approximately 85% are living with overweight or obesity. In the Netherlands, over one million people already have T2D, and it has been estimated that one out of every three Dutch adults will develop T2D in his or her life [1, 2]. When a person has the combination of both T2D and obesity, he or she will have more complications and an increased risk of cardiovascular disease and mortality [3].

Weight loss alleviates this problem and improves cardiovascular risk profile and quality of life and reduces the risk of more than 200 other obesity-related diseases [4]. Our previous study showed that a diet program based on a very low energy diet (VLED) led to long-term weight loss (2 years), improved quality of life, improvement in depressive symptoms, and a lower need for insulin in patients who have had T2D for a long time [5]. A VLED is a diet that contains 400–800 kcal per day, with two meal replacements with adequate protein intake [6]. An evaluation of the program demonstrated that 95% of participants would recommend the program to others. The DiRECT trial showed similar results for a VLED intervention after 2 years in patients with recently diagnosed T2D: a decrease in mean body weight and improved quality of life for patients in the intervention group [7].

However, sustainable weight loss is difficult to achieve without professional help, and with the growing rates of T2D and obesity, the pressure on our health care system increases in terms of morbidity and costs [8]. In order to be successful, lifestyle intervention programs need to be of high intensity (with frequent contacts) and multidisciplinary, making them costly and limited to available human resources [9, 10].

eHealth-based treatments are a promising tool to provide dietary support at a lower cost than face-to-face interventions, especially when extended follow-up is needed. The term eHealth, is defined by Eysenbach et al. “eHealth refers to health services and information delivered or enhanced through the Internet and related technologies. Moreover, eHealth applications may increase access, improve convenience, and increase participant engagement [11–13]. However, eHealth interventions seem less effective in producing weight loss than face-to-face “in-person” treatment [14–16]. Among people with T2D, there is a great deal of variation in the type of eHealth used in dietary interventions. In general, the use of eHealth alone is less effective in reducing weight. Combining a diet program with the use of some form of eHealth is more effective in terms of weight loss.

Hypothetically, blended care with the combination of in-person treatment and eHealth solutions, is the most (cost)effective [12]. However, the (cost)effectiveness of an E-VLED weight loss intervention in people with T2D has not been studied to date.

## Objectives {7}

The primary objectives of this study are as follows:To determine if an E-VLED intervention is equally effective as the usual care VLED in reducing weight after one year in people with T2D and obesity, andTo determine if an E-VLED intervention is lower in costs than the usual care VLED.

The secondary objectives of this study are as follows:To determine the effectiveness of an E-VLED intervention regarding cardiovascular risk factors and quality of life, compared to a VLED interventionTo determine the effectiveness of an E-VLED intervention regarding patient satisfaction and attrition/compliance, compared to a VLED interventionTo determine if there is a difference in effectiveness and patient satisfaction of an E-VLED intervention between males and femalesTo determine if there is a difference in effectiveness and patient satisfaction of an E-VLED intervention between participants of different origins

### Trial design {8}

This study is a randomised, controlled, non-inferiority multi-centre trial with a duration of 1 year. After signing informed consent, eligible participants will be randomised 1:1 to the intervention (E-VLED) or control (VLED) group. Outcome parameters will be measured at baseline, 2 months, 4 months, and at 1 year. In Fig. 1, we show the flow chart of this study.

**Fig. 1 Fig1:**
[figure not shown]
Flow chart of the trial

## Methods: participants, interventions, and outcomes

### Study setting {9}

Patients with T2D and obesity will be recruited from the Diabetes outpatient clinic of the University Medical centre, Erasmus MC, of the Ikazia hospital, and dietician practice HRC, all located in Rotterdam, The Netherlands.

### Eligibility criteria {10}

Inclusion criteria.Type 2 diabetesAge 18–75 yearsOverweight/obesity (BMI ≥ 27 kg/m.^2^)Smartphone with Android or iOS

Exclusion criteria.Pregnancy or lactation during the studyInsufficient command of the Dutch language, spoken or written assessed in the intake interviewSevere psychiatric problems, use of antipsychotic drugsSignificant cardiac arrhythmias; unstable angina; decompensated congestive heart failure; carcinomas; major organ system failure; untreated hypothyroidism; end-stage renal diseaseMyocardial infarction, cerebrovascular accident, or major surgery during the previous 3 monthsOther types of diabetesSubstantial wounds like diabetic footUsing glucagonlike peptide-1 (GLP-1) medication for < 3 months

The appointments and intervention will be performed by a researcher/dietician specialised in diabetes and lifestyle.

### Who will take informed consent? {26a}

Patients will be given at least two weeks to decide whether they want to participate after they receive the information by the research coordinator. Inclusion is complete after the participant and the researcher sign the informed consent form.

### Additional consent provisions for collection and use of participant data and biological specimens {26b}

We ask for informed consent for the collection of one tube of blood for biobanking, in order to answer future research questions.

### Interventions

#### Explanation for the choice of comparators {6b}

In people with T2D and overweight/obesity, the use of a VLED intervention has been shown to be effective in achieving weight reduction and reducing cardiovascular risk. However, the current method of counselling is very labour-intensive and time-consuming and limited to people who can regularly visit the hospital. By using eHealth, this problem may be solved. Therefore, we want to compare a VLED in its current face-to-face counselling form with the same VLED in which part of the face-to-face contacts are replaced using a mobile application.

### Intervention description {11a}

#### The control and intervention group

Both groups will receive a VLED, with meal replacements (The 1:1 diet by Cambridge Weight Plan®), plus a stepped care approach to reintroduce a healthy and sustainable long-term diet according to national guidelines [17]. Patients will follow a VLED of approximately 3140 kJ (750 kcal)/day for 10 weeks, consisting of two meal replacements plus 75 g of lean meat/fish/vegetarian replacement, 150 ml skimmed milk, and low-energy drinks and low-carbohydrate vegetables ad libitum.

After 10 weeks, the diet is changed into a low-calorie diet of 4600–5400 kJ (1100–1300 kcal)/day, gradually increasing the intake during the following 12 weeks. After a total of 22 weeks, the participants use a diet based on national health recommendations, aimed at weight maintenance. During the entire intervention, 60 min of exercise per day is advised. We encourage long-term behavioural change by making use of behavioural therapy techniques (among others: goal setting, identifying barriers and self-monitoring). During the diet, glucose levels (fasted and postprandial) are monitored (via phone) and glucose lowering agents are adjusted accordingly, by the dieticians, diabetes nurses, and medical doctor. Moreover, antihypertensive medication is adjusted whenever the blood pressure becomes too low due to the weight loss. The process is guided by registered dieticians of the University Medical centre, Erasmus MC in Rotterdam, and dietician practice HRC.

#### The intervention group

The eHealth application, which replaces part of the face-to-face contacts, will only be used by the intervention group. In-person contact will be limited to one individual intake meeting and three group meetings. The eHealth application is a mobile diet app, which was developed earlier and has already been pilot tested. In this app, the steps of the diet-intervention will be explained via text and infographics. Participants will receive recipes and tips useful for the different stages of the diet. Exercise is encouraged with personal goal setting, using the national guidelines for exercise [18], and challenges. Personal goal setting with respect to diet, exercise, weight, body composition, glucose levels, medication use, physical complaints, and quality of life will be used and monitored within the app. Moreover, participants will receive daily motivational messages to keep them on-track. To make the app more interactive, the participants can use a chat-function with the dietician, once a week for the first 10 weeks; thereafter, the dietitian will be available every other week for the chat feature in the app. The app is end-to-end encrypted, according to the national privacy guidelines.

#### The control group

In this group, the participants will follow the VLED intervention and will receive one individual intake meeting, five group meetings, and four planned contact moments by mail or phone (more whenever it is necessary for glucose regulation). In this group, the motivational aspect and personal goal setting with respect to diet, exercise, weight, body composition, glucose levels, medication use, physical complaints, and quality of life will be monitored during the group meetings.

### Criteria for discontinuing or modifying allocated interventions {11b}

Subjects can leave the study at any time for any reason if they wish to do so, without any consequences. The investigator can decide to withdraw a subject from the study for urgent medical reasons. We will analyse the study results according to the intention-to-treat principle; withdrawn participants will not be replaced.

Patients who withdraw from the study will be asked (voluntarily) about their reasons for withdrawal and will receive the usual treatment of the diabetes medical team.

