### Plans to promote participant retention and complete follow-up {18b}

Patients will receive a notification in the app (intervention group) or via mail (control group) of research appointments. They will also be notified if questionnaires are not completed on time. Also, when patients are not active in the app for the first 1 to 2 weeks, the patient is contacted to see if there is an issue with the app that can be resolved. When patients do not show up for their appointments, they will be contacted by phone to find out the reason for their absence. Their appointment will be rescheduled if possible.

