### Methods in analysis to handle protocol non-adherence and any statistical methods to handle missing data {20c}

Data will be analysed based on the intention-to-treat principle. The general linear model takes drop out under the missing at random assumption into account.

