### Adverse event reporting and harms {22}

Adverse events are defined as any undesirable experience occurring to a subject during the study, whether considered related to the investigational product/study procedure/the experimental intervention. All adverse events reported spontaneously by the subject or observed by the investigator or his staff will be recorded.

A serious adverse event is any untoward medical occurrence or effect that.-Results in death;-Is life threatening (at the time of the event);-Requires hospitalisation or prolongation of existing inpatients’ hospitalisation;-Results in persistent or significant disability or incapacity;-Any other important medical event that did not result in any of the outcomes listed above due to medical or surgical intervention but could have been based upon appropriate judgement by the investigator.

An elective hospital admission will not be considered as a serious adverse event.

The investigator or anyone from the medical staff to whom the adverse event is reported will immediately inform the principal investigator who in his turn will inform the sponsor (head of the Department of Internal Medicine).

The investigator will report all SAEs to the sponsor without undue delay after obtaining knowledge of the events.

The sponsor will report the SAEs through the web portal ToetsingOnline to the accredited METC that approved the protocol, within 7 days of first knowledge for SAEs that result in death or are life threatening followed by a period of maximum of 8 days to complete the initial preliminary report. All other SAEs will be reported within a period of maximum 15 days after the sponsor has first knowledge of the serious adverse events.

All AEs will be followed until they have abated or until a stable situation has been reached. Depending on the event, follow-up may require additional tests or medical procedures as indicated and/or referral to the general physician or a medical specialist.

SAEs need to be reported till end of study within the Netherlands, as defined in the protocol.

[data safety monitoring board (DSMB)/safety committee].

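### Section {11b} makes an urgent medical reason a withdrawal from the study rather than from the intervention, so week-52 weight and costs are not secured for these patients

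*Protocol article*

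**What the plan says.** In the protocol article, section {11b} (Criteria for discontinuing or modifying allocated interventions) names two routes, and both lead out of the study. For the participant: "Subjects can leave the study at any time for any reason if they wish to do so, without any consequences". For the investigator: "The investigator can decide to withdraw a subject from the study for urgent medical reasons". The section describes no status in which the allocated intervention has ended but the patient remains in follow-up.

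On what happens next, with care passing back to the diabetes team, it says: "Patients who withdraw from the study will be asked (voluntarily) about their reasons for withdrawal and will receive the usual treatment of the diabetes medical". It mentions no outcome visit after withdrawal. It also sets the analysis principle: "We will analyse the study results according to the intention-to-treat principle; withdrawn participants will not be replaced".

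Four other sections bear on this:

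- Missing data {20c}: "The general linear model takes drop out under the missing at random assumption into account".
- Adverse events {22}: "All AEs will be followed until they have abated or until a stable situation has been reached", and "SAEs need to be reported till end of study within the Netherlands, as defined in the protocol".
- Retention {18b}: "When patients do not show up for their appointments, they will be contacted by phone to find out the reason for their absence". This covers missed appointments; withdrawn patients are not mentioned.
- Outcomes {12} and Table 1: the main outcomes are percentage weight change at 1 year and costs. Weight and TiC-P are both scheduled at start, week 10, week 20 and week 52.

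**The concern.** Stopping an intervention and leaving a study are different events, and an intention-to-treat comparison depends on keeping them apart. If {11b} is followed as written, a medical reason for ending the intervention also ends participation, and the week-52 weight and later TiC-P may go uncollected.

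This missingness would be created by a decision of the investigator, who is not blinded ({17a}), and it would be tied to the patient's medical course. That is where missing at random is hardest to defend. Costs are also exposed: they include health-care use and production losses, and patients with urgent medical problems may be among the more expensive. Section {20a} already expects the cost data to be skewed, and losing these patients could thin the upper tail.

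The trial is a non-inferiority comparison of two ways of delivering the same diet with different amounts of personal contact. Unequal withdrawal between arms cannot be ruled out.

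**Working it through.** **1. The plan's own sample size.** Inputs from {14}: SD 7.2%, margin 3, assumed true difference 2 in favour of the intervention, one-sided alpha 0.025, power 0.80.

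n per arm = 2 × (1.960 + 0.842)² × 7.2² / (3 + 2)² = 2 × 7.85 × 51.84 / 25 = 32.6, rounded up to 33. This matches the stated 33. With 40 per arm and 20% drop-out, 0.20 × 40 = 8 are lost and 32 remain. The plan thus counts drop-outs as giving no 12-month weight, which agrees with {20c} treating drop-out as missing data.

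**2. Who falls out of the primary model.** The dependent variable in {20a} is relative weight change at the post-baseline time points. The model contains arm, time point, hospital and the arm-by-time interaction. Table 1 places the first post-baseline weight at week 10. (Trial design {8} gives 2 months, and {20a} calls the 12-month point T3 where Table 1 has T4; neither difference alters the argument.)

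- Withdrawn before the first post-baseline weight: no value of the dependent variable exists, so the patient contributes nothing. This window covers the 10-week VLED phase described in {11a}.
- Withdrawn later: the earlier weights are used, and week 52 is in effect predicted from patients of the same arm who stayed.

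**3. Possible shift in the primary estimate.** Let w be the excess share of one arm that is withdrawn, and d the gap between these patients' true week-52 change and what the model implies for them. The arm mean, and so the between-arm difference, is off by w × d. The documents give neither input, so both are assumptions.

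- w = 5% (2 of 40), d = 5: 0.05 × 5 = 0.25 points, 8% of the margin.
- w = 10% (4 of 40), d = 5: 0.10 × 5 = 0.5 points, 17% of the margin.
- w = 10%, d = 7: 0.10 × 7 = 0.7 points, 23% of the margin.
- Wider range, w from 2.5% to 20% and d from 2 to 10: from 0.025 × 2 = 0.05 to 0.20 × 10 = 2.0 points. The upper end needs an excess as large as all 8 expected drop-outs in one arm.

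Direction: if the withdrawn patients are in the E-VLED arm and do worse than predicted, the estimate is too favourable to E-VLED. If they are in the control arm, it errs the other way.

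**4. Precision.** Under the {14} assumptions and a normal approximation, power is 79.3% at 32 per arm, 80.5% at 33 and 83.8% at 36. One retained patient per arm restores the planned 33. Retaining half of all expected drop-outs (36 per arm) would cut the standard error by 1 − √(32/36) = 5.7%. That counts voluntary leavers as well as medical withdrawals and ignores the earlier weights the model already uses, so it is an upper guide.

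**5. Costs.** No comparable calculation is possible, because the documents give no cost figures.

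**The case against.** The strongest reply is that this is a journal article condensing a fuller protocol (version 4) that is not shown. Section {11b} does not say that measurement stops at withdrawal, and procedures after withdrawal are the kind of detail an article leaves out. This stands in part. A reader might infer that the data are lost; the text supports only that they are not secured. The point survives because {11b} is not silent: it states an action, and that action merges ending the intervention with leaving the study.

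A reader might also infer that safety data vanish after a medical withdrawal. The documents do not support this. Section {22} exempts no withdrawn patient, so the event behind the withdrawal is still followed, and patients return to the diabetes team. What remains is narrower: {22} relies on events the patient reports or staff observe, and {11b} sets out no contact for the study after withdrawal, so the two sections should be reconciled for new events.

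A third tempting reading is that {11b} breaks the plan's own intention-to-treat rule. It does not. Nothing removes withdrawn patients from their randomised arm, their available weights are used, and missing at random is stated openly. The weakness is dependence on that assumption, together with the loss of patients who have no post-baseline weight.

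Nor can one infer how a pregnancy arising during the study would be handled: {10} lists it as an exclusion, and no on-study rule is given.

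Finally, poor adherence is measured separately from attrition ({18a}), and both arms follow the same diet, so a large imbalance in medical withdrawals is not obviously expected. An excess of 2 to 4 patients would equal 25 to 50% of one arm's 8 expected drop-outs. This stands, and it keeps the likely effect modest.

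**Conclusion.** The point holds as a cheap improvement. As written, {11b} turns an urgent medical reason into withdrawal from the study and leaves the week-52 weight and TiC-P unsecured for these patients. Early withdrawals drop out of the primary model; later ones depend on missing at random where it is least secure.

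The size is unknown. The illustrative 0.25 to 0.7 points against a 3-point margin rests on an assumed excess of 5 to 10% in one arm and an assumed gap of 5 to 7 points; neither figure comes from the documents. A shift of that order would matter mainly if the upper confidence limit fell close to the margin. The effect on power is small. Loss of safety data and breach of intention-to-treat are not established.

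**What to change.** In {11b}, separate two events: the end of the allocated intervention, and leaving follow-up. State that, whatever the reason the intervention ends, the week-52 weight and TiC-P already in Table 1 are still collected unless the patient declines. When a patient leaves, ask separately whether a final weight and cost questionnaire remain acceptable. Reconcile {11b} with {22}, so that AE follow-up and SAE reporting to end of study clearly apply to these patients. The wording should not touch on when the diet is stopped or changed.

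If the full protocol already says this, one sentence in the article is enough. Otherwise the cost is one paragraph and an off-intervention status in the case report form. No visit is added, since week 52 is already scheduled. The downside is some effort to reach patients who have stopped the intervention. With recruitment estimated to end on 1 July 2023 ({Trial status}) and 52 weeks of follow-up, the last week-52 visits would fall around mid-2024, after the article's publication in October 2023, so the change could still have protected some data at that point.
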